# Effects of high-frequency transcranial magnetic stimulation on functional performance in individuals with incomplete spinal cord injury: study protocol for a randomized controlled trial

**DOI:** 10.1186/s13063-017-2280-1

**Published:** 2017-11-06

**Keywords:** Incomplete spinal cord injury, Plasticity, Motor rehabilitation, Non-invasive brain stimulation, Repetitive transcranial magnetic stimulation

## Abstract

**Background:**

Repetitive transcranial magnetic stimulation (rTMS) has been investigated as a new tool in neurological rehabilitation of individuals with spinal cord injury (SCI). However, due to the inconsistent results regarding the effects of rTMS in people with SCI, a randomized controlled double-blind crossover trial is needed to clarify the clinical utility and to assess the effect size of rTMS intervention in this population. Therefore, this paper describes a study protocol designed to investigate whether the use of rTMS can improve the motor and sensory function, as well as reduce spasticity in patients with incomplete SCI.

**Methods:**

A double-blind randomized sham-controlled crossover trial will be performed by enrolling 20 individuals with incomplete SCI. Patients who are at least six months post incomplete SCI (aged 18–60 years) will be recruited through referral by medical practitioners or therapists. Individuals will be randomly assigned to either group 1 or group 2 in a 1:1 ratio, with ten individuals in each group. The rTMS protocol will include ten sessions of high-frequency rTMS (5 Hz) over the bilateral lower-limb motor area positioned at the vertex (Cz). Clinical evaluations will be performed at baseline and after rTMS active and sham.

**Discussion:**

rTMS has produced positive results in treating individuals with physical impairments; thus, it might be promising in the SCI population. The results of this study may provide new insights to motor rehabilitation thereby contributing towards the better usage of rTMS in the SCI population.

**Trial registration:**

ClinicalTrials.gov, NCT02899637. Registered on 25 August 2016.

**Electronic supplementary material:**

The online version of this article (doi:10.1186/s13063-017-2280-1) contains supplementary material, which is available to authorized users.

## Background

Spinal cord injury (SCI) affects about 2.5 million individuals worldwide and often leads to severe disability, due to functional limitations in the sensory and motor systems [1]. After trauma or pathological processes upon the spinal cord, there is usually some preservation of sensation, or motor function at the lowest segment of the spinal cord, a condition known as incomplete SCI (iSCI) [2]. iSCI has been associated with a serious reduction in quality of life and functional independence [3, 4]. Therefore, effective rehabilitation programs are required for patients with iSCI in both acute and chronic care.

Processes of neural regeneration and plasticity can result in significant functional recovery after iSCI [5]. Spontaneous recovery of motor and sensory function in iSCI individuals can be substantial, but highly variable [6]. Repetitive transcranial magnetic stimulation (rTMS) rehabilitation techniques, based on protocols that selectively stimulate specific pathways along the central nervous system (CNS), have been found to be effective in enhancing neurological recovery leading to improved functional abilities [7]. rTMS is a procedure that involves repetitively delivering biphasic magnetic pulses over a specific cortical site [8, 9] to provide stimulation of the corticospinal tract (CST), primary motor cortex (M1), and spinal cord, so as to induce neuronal reorganization, which can be largely involved in the control of voluntary movements [10].

Protocols involving rTMS have been used to induce changes in the excitability of neuronal circuits with positive effects [11–16] at the site of stimulation or transsynaptically at distant sites such as spinal cord circuits [17, 18]. The effect of high-frequency rTMS (i.e. ≥ 5Hz) includes changes in synaptic plasticity resembling long-term potentiation (LTP), as well as shifts in network excitability, activation of feedback loops, and activity-dependent metaplasticity [19, 20]. On this basis, rTMS is emerging as a promising technique in improving neurophysiological outcomes and voluntary motor output in patients with motor disorders [11, 21, 22]. Indeed, studies indicate that motor improvements may be due to modification of corticospinal projections by increasing motor cortical excitability [14–16] and, consequently, promote plasticity associated with functional recovery [22]. Additionally, reduction in spasticity may occur through enhancement of descending corticospinal projections and segmental effects on spinal interneurons that might strengthen inhibitory connections [13, 14, 23].

Many studies have used rTMS as a non-invasive and painless method to induce long-lasting changes in the excitability of cortical and corticospinal pathways after iSCI. In this scenario, rTMS has been found effective in enhancing corticospinal synaptic transmission [12], reducing spasticity [13, 14, 23] and improving sensorimotor function after iSCI [14–16], although we note none of these studies reported associated effect sizes in their analyses. However, other studies report less positive findings, including unchanged sensorimotor function [24], as well as unaltered cortical excitability and level of spasticity [16] in response to rTMS. The lack of consistent results is likely associated with differences in stimulation parameters (e.g. intensity, frequency, number of pulses), number of sessions, relative location of M1, chronicity and levels of injury, and outcome measurements used in previous studies [10].

In considering three particular studies that have examined the effects of rTMS in individuals with iSCI, we note interesting results on sensory and motor performance. Belci et al. [15] delivered double pulses of rTMS over the M1 representation of thenar muscles (360 doublets, separated by 100 ms). They used a low frequency (with 10 s between each doublet and stimulus intensity corresponding to 90% of resting motor threshold [RMT]) for five days in a group of four individuals with iSCI. Results indicated that active rTMS improved somatosensory and motor function at three weeks following stimulation, as assessed by the American Spinal Injury Association Impairment Scale (ASIA) nine-hole peg test and electrical perceptual threshold measurements. Additionally, Benito et al. [14] applied 15 sessions of sham or rTMS over the leg representation of M1 (20 trains of 40 pulses at 20 Hz with an intensity of 90% of RMT) in 17 individuals with iSCI. This study found significant improvements in motor function for at least two weeks, as assessed by the ASIA scale for lower limbs and gait function. Contrary to the findings noted above, ASIA scores were unaltered in Kuppuswamy et al. [24]. The protocol had five days of active or sham rTMS (900 pulses at 5 Hz in 2 s trains separated by 80-s intervals, at 80% of active motor threshold) applied to M1 representations of either the hand or forearm muscles in 15 individuals with iSCI. It is worth noting that the studies cited above have reported sham placebo-controlled trials which were single-blinded [15, 24], non-randomized [15], and either all [15, 24], or at least part of the individuals crossed over between groups during the study [14].

Therefore, while there is good evidence for its use in other diseases, the literature regarding the efficacy of rTMS in individuals with iSCI is inconsistent, as the few studies that have addressed this issue yielded contrasting results. Due to the quality of the study design as well as to the differences in rTMS parameters used in previous studies, there is no strong evidence of consistent changes in sensory and motor function in individuals with iSCI after rTMS [10]. Thus, there are gaps in the knowledge base and hence the development of a new prospective study, with a fully randomized double-blind placebo-controlled design [25], is necessary to provide evidence of the clinical utility of rTMS in individuals with iSCI. Due to the positive effects of rTMS in inducing long-lasting changes in spinal and supraspinal circuits, we hypothesized that rTMS applied over the lower-limb motor area will: (1) improve motor function; (2) improve sensory function; and (3) reduce spasticity.

Therefore, our aim was to identify a protocol for a double-blind randomized controlled crossover trial that will be performed to evaluate the effects of high-frequency rTMS on the sensorimotor function and spasticity in individuals with iSCI.

## Methods/Design

We registered this trial on ClinicalTrials.gov (NCT02899637). This paper has been reported in accordance with the Standard Protocol Items: Recommendations for Interventional Trials (SPIRIT) [26].

### Study design

A double-blinded randomized controlled crossover trial will be conducted and all participants will undertake rTMS-active and sham. Group 1 will start with five sessions of rTMS-active. After two weeks, this group will be reallocated to five sessions with rTMS-sham. In contrast, group 2 will do the opposite protocol (participants will start allocated to five sessions of rTMS-sham, and after a two-week washout period will be reallocated to five sessions of rTMS-active). The two-week washout period has been used in some studies [24, 27] and was shown to be enough to reset the effects of the first five sessions, considering that the motor effects of the rTMS in individuals with iSCI are sustained for 1 h [24] to two weeks [14] and that spasticity effects endure for one week [16, 23]. Figure 1 summarizes the planned experimental design. This research protocol follows the SPIRIT recommendations. For the SPIRIT Checklist see Additional file 1 and for the SPIRIT Figure see Fig. 2. Table 1 provides an overview of the trial characteristics, based on the WHO Trial Registration Data Set.

**Fig. 1 Fig1:**
[figure not shown]
*Flowchart* for the rTMS study protocol. The participants will be selected and the eligibility assessment will be applied. They will then be randomized and allocated to group 1 (starting with rTMS-active) or group 2 (starting with rTMS-sham). Five sessions of rTMS-active and sham will be applied to participants in each group over one week, with a washout period (two weeks). Assessments will be before and after each intervention period (i.e. sham and active) using the motor and sensory scales, spasticity scale, and surface electromyography

**Fig. 2 Fig2:**
[figure not shown]
SPIRIT figure. Description of the rTMS study protocol

**Table 1 Tab1:** Trial characteristics based on WHO Trial Registration Data Set

Data category	Trial information
Primary registry and trial identifying number	ClinicalTrials.gov, ID: NCT02899637
Date of registration in primary registry	25 August 2016 on
Secondary identifying numbers	Ethical Committee of Paraiba State University, under the number CAEE: 18753713.0.0000.5187
Source(s) of monetary or material support	Foundation of Support for Research of São Paulo State - FAPESP #2015/13096-1 and Coordination for Higher Education Staff Development - CAPES.
Primary sponsor	University of Sao Paulo – USP
Secondary sponsor(s)	NA
Contact for public queries	[name], [name]
Contact for scientific queries	[name], [name]
Public title	Effects of transcranial magnetic stimulation on incomplete spinal cord injury
Scientific title	Effects of high-frequency transcranial magnetic stimulation on functional performance in individuals with incomplete spinal cord injury: study protocol for a randomized controlled trial
Country of recruitment	Brazil
Health condition(s) or problem(s) studied	Spinal cord injury
Interventions	High-frequency repetitive transcranial magnetic stimulation on the lower-limb area of the motor cortex, over one week (five consecutive sessions – once a day)
Key inclusion and exclusion criteria	Inclusion criteria: clinical diagnosis of iSCI with non-progressive etiology; at least six months post iSCI; clinical stability; age range 18–60 years; satisfactory score in Scale of Mini-Mental State Examination (i.e. cut-off points of 13 for illiterates, 18 for low and middle school, and 26 for high school); no pathological alterations on electroencephalography; absence of depression as assessed by the Hamilton Depression Scale and receive sensorimotor conventional physiotherapy. Exclusion criteria: metal prosthesis in some part of the body; cardiac pacemaker; either cognitive impairment, psychotic, or either schizophrenic disorders; neuropsychiatric co-morbidity; drugs that reduce seizure threshold or spasticity
Study type	Interventional allocation: randomized
	Masking: double-blind
	Assignment: crossover
	Primary purpose: treatment
Date of first enrolment	December 2017
Target sample size	20
Recruitment status	Recruiting
Primary outcome(s)	Change in motor scores from baseline to four weeks
Key secondary outcome(s)	Assessment of change in sensory and spasticity scores from baseline to four weeks

*NA* not available

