### Randomization

Participants will be randomly allocated to either group 1 (rTMS-active) or group 2 (rTMS-sham) with a 1:1 allocation defined by a computer-generated randomization using the R package (R Foundation for Statistical Computing) [32]. Randomization will be under the control of a blinded investigator who will be the only person allowed to manage the electronic security file of the randomization to assign the individuals. The investigator will be blind to the group in which the participant is allocated to.

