#### Data analysis

The analysis will follow a pre-specified analysis plan, based on comparing the groups as randomized (intention-to-treat). All data will be presented as mean ± standard deviation and summarized in frequency tables. We will use Microsoft Office Excel for Windows (version 2013) to store the data and the Statistical Package for Social Sciences (SPSS-IBM®) version 21 for Windows to perform statistical analysis. The normality and homogeneity of all variables (i.e. primary and secondary outcomes) will be tested with the Shapiro–Wilk and Levene’s test, respectively. For non-parametric data, the Friedman test will be used followed by the Wilcoxon post hoc test. We will use the ANOVA two-way (2 × 4) for the inferential statistic of the parametric data, with Tukey’s post hoc tests. Significance level will be set as α ≤ 0.05 and the effect size will be calculated by eta-squared (*ŋ*
^*2*^).

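### The stated primary and key secondary outcomes run from baseline to four weeks, the end of period 2, when every participant has had both active and sham; no within-period active-minus-sham outcome is defined

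*Protocol article*

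**What the plan says.** - **Outcome and time frame.** Table 1 lists the primary outcome as "Change in motor scores from baseline to four weeks" and the key secondary outcomes as "Assessment of change in sensory and spasticity scores from baseline to four weeks".
- **Schedule.** The Fig. 1 legend has five sessions given to "participants in each group over one week, with a washout period (two weeks"), and assessments before and after each intervention period. Under Study design, "all participants will undertake rTMS-active and sham".
- **Sequences.** For one group, "Group 1 will start with five sessions of rTMS-active. After two weeks, this group will be reallocated to five sessions with rTMS-sham". The other starts on sham and "after a two-week washout period will be reallocated to five sessions of rTMS-active".
- **Labels.** The Randomization section says participants will be "randomly allocated to either group 1 (rTMS-active) or group 2 (rTMS-sham"). This names each group by its first treatment only.
- **Outcome in the text.** The Primary outcomes section refers to change from baseline in the ASIA motor values. It gives no time point, no period baseline and no comparison of active with sham.
- **Analysis.** The Data analysis section is "based on comparing the groups as randomized (intention-to-treat"), with a 2 × 4 two-way ANOVA for parametric data and a Friedman test with Wilcoxon post hoc tests otherwise.

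**The concern.** The case for a crossover is that each participant supplies a change under active and a change under sham, and the treatment effect is the difference between them. An outcome measured from the start of the study to the end of the second period is a single number per participant, taken after both treatments. It cannot hold that difference. What it estimates depends on how it is then summarised, and none of the available summaries is the comparison for which the crossover was chosen.

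At stake are the meaning and the precision of the main result in a trial of 20 participants.

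**Working it through.** **Timing.** 1 week (period 1) + 2 weeks (washout) + 1 week (period 2) = 4 weeks. The stated time point is the end of period 2.

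**What the week-4 change estimates.** Let tau be the active-minus-sham effect, p the sham response plus time trend (taken as equal in both groups), and c the fraction of tau that a participant treated first with active still carries at week 4.

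- Group 1 (active then sham): c·tau + p
- Group 2 (sham then active): tau + p
- All participants pooled: (1 + c)·tau/2 + p
- Group 1 minus group 2: c·tau − tau = −(1 − c)·tau

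With tau = 0.65, the standardised effect in the Sample size section:

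| c | Group 1 − group 2 | Pooled change |
|---|---|---|
| 0 (the washout the protocol assumes) | −0.65 | 0.325 + p |
| 0.25 | −0.49 | 0.406 + p |
| 0.5 | −0.33 | 0.488 + p |
| 1 | 0 | 0.65 + p |

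The pooled or within-group change cannot be separated from p. The between-group contrast is free of p. It has size tau when c = 0 and shrinks as c grows. Its sign is negative for a beneficial treatment if group 1 is read as the active arm.

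**Precision.** The documents give no variance, so the following is assumed: a participant effect plus independent residuals of SD 1 at each assessment, 10 participants per sequence, no carryover, and a two-sided 5% t test with 18 degrees of freedom.

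- Week-4 contrast: each change has variance 1 + 1 = 2, so SE = √(2/10 + 2/10) = 0.632.
- Within-participant comparison of within-period changes: each period's change has variance 2, and the difference between periods has variance 4. The estimate is half the difference in its mean between sequences, so SE = ½·√(4/10 + 4/10) = 0.447.

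| Assumed effect (residual SDs) | Week-4 contrast: effect/SE, power | Within-period changes: effect/SE, power |
|---|---|---|
| 1.30 | 2.06, 49% | 2.91, 78% |
| 0.65 | 1.03, 16% | 1.45, 28% |

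The value 1.30 corresponds to the protocol's 0.65 if that figure is standardised by the SD of a participant's active-minus-sham difference in change, which is √4 = 2 here (0.65 × 2 = 1.30). The second row takes 0.65 directly in residual SDs. The protocol does not say which scale applies, so both are shown. In either case the week-4 contrast has twice the variance (0.40 against 0.20).

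**Does the planned ANOVA supply the contrast?** Read as 2 groups × 4 assessments, with full washout and apart from common trend, the expected profiles are (0, tau, 0, 0) for group 1 and (0, 0, 0, tau) for group 2. Each averages tau/4, so the group main effect is zero. The treatment signal lies in the group-by-time interaction, which the protocol does not name as the test of the primary outcome.

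**The case against.** Table 1 is a registry-style overview, and four weeks is the length of the whole trial, so the phrase may have been meant as the follow-up window. Assessments around each period are planned, and the four levels of the ANOVA match them. No section says that a two-group test of week-4 change will be the primary analysis, and the detailed contrast may sit in an analysis plan that is not shown. This stands in part: the data collection is sound, and the interaction in the 2 × 4 model does carry the treatment effect. It does not dispose of the point, because the article states an outcome with a time frame, that statement does not fit the design, and no section corrects it. A plan that used within-period changes would depart from the published primary outcome.

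Three stronger readings are tempting and are not supported.

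- **That the outcome cannot isolate the rTMS effect at all.** Under the washout assumed in Study design, the week-4 difference between sequences has absolute size tau. It is a valid, though inefficient, comparison of active with sham in period 2.
- **That the result will come out reversed.** This requires an analyst to take the Randomization labels literally. Study design and the Fig. 1 legend set out both sequences clearly.
- **That a real benefit will appear as zero.** This needs the whole effect to persist to week 4, whereas Study design puts motor effects at between one hour and two weeks.

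A reader might also set the 49% against the 97% obtained by testing post-treatment scores only (SE 0.316 under the same assumptions, effect 1.30). That is not the comparison for an outcome defined as change; 78% is.

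**Conclusion.** The point holds as a mismatch between the stated outcome and the crossover design. The time frame in Table 1 ends after both treatments, and neither the Primary outcomes nor the Data analysis section defines a within-period change or an active-minus-sham contrast.

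Taken literally, the outcome gives either a change confounded with sham response and trend, or a period-2 comparison with twice the variance of the within-participant one. The power loss is from about 78% to 49%, or from 28% to 16%, depending on the scale of the effect. These figures rest on the assumed residual SD of 1, independent residuals, no carryover and no dropout. The timing argument and the expected values need none of the variance assumptions. The sign problem is one of labelling and disappears once the groups are named as sequences.

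**What to change.** - In Table 1 and the Primary outcomes section, define the motor outcome as the within-participant active-minus-sham difference in change from the assessment immediately before to the one immediately after each five-session period. Estimate it with a period term. Define the sensory and Modified Ashworth outcomes in the same way.
- Mention four weeks only as the total length of follow-up.
- In the Randomization section, name the groups active-then-sham and sham-then-active.

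The cost is wording. The assessments in the Fig. 1 legend already provide the data, with no extra visits. As the Trial status section says recruitment has begun, the change should be dated and made before unblinding.

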### Participants and sampling

Participants will be recruited through referral by medical practitioners or therapists who work at the Physiotherapy Health Center of Paraíba State University in Brazil in single-stage cluster sampling. Those interested in participating will undergo a detailed screening against the eligibility criteria for enrollment in the study.

### Inclusion criteria

Participants will be included if they have agreed to participate in the study and have signed an informed consent form. They will have a clinical diagnosis of iSCI with non-progressive etiology which is characterized by spinal, vascular, and infectious trauma. Neuroimaging examinations, such as computed tomography and nuclear magnetic resonance imaging, will be used to exclude SCIs due to progressive worsening conditions such as neurodegenerative, tumor, and demyelinating pathologies [28, 29]. The participants should be at least six months post iSCI, clinically stable, aged 18–60 years, have a satisfactory score in Scale of Mini-Mental State Examination (MMSE) (i.e. cut-off points of 13 for illiterates, 18 for low and middle school, and 26 for high school), have no pathological alterations on electroencephalography (EEG), be clear of depression as assessed by the Hamilton Depression Scale (HAM-D), and be currently receiving conventional sensorimotor physiotherapy, to a maximum of three times per week.

